## Abstract

**Background:**

The COVID-19 pandemic and resultant restrictions on social gatherings significantly impacted many peoples’ sense of social connectedness, defined as an individual’s subjective sense of having close relationships with others. Older adults living in long-term care homes (LTCHs) experienced extreme restrictions on social gatherings, which negatively impacted their physical and mental health as well as the health and well-being of their family caregivers. Their experiences highlighted the need to reconceptualize social connectedness. In particular, the pandemic highlighted the need to explore novel ways to attain fulfilling relationships with others in the absence of physical gatherings such as through the use of a hybridized system of web-based and in-person presence.

**Objective:**

Given the potential benefits and challenges of web-based presence technology within LTCHs, the proposed research objectives are to (1) explore experiences regarding the use of web-based presence technology (WPT) in support of social connectedness between older adults in LTCHs and their family members, and (2) identify the contextual factors that must be addressed for successful WPT implementation within LTCHs.

**Methods:**

This study will take place in south western Ontario, Canada, and be guided by a qualitative multimethod research design conducted in three stages: (1) qualitive description with in-depth qualitative interviews guided by the Technology Acceptance Model (TAM) and analyzed using content analysis; (2) qualitative description and document analysis methodologies, informed by content and thematic analysis methods; and (3) explicit between-methods triangulation of study findings from stages 1 and 2, interpretation of findings and development of a guiding framework for technology implementation within LTCHs. Using a purposeful, maximum variation sampling approach, stage 1 will involve recruiting approximately 45 participants comprising a range of older adults, family members (30 participants) and staff (15 participants) within several LTCH settings. In stage 2, theoretical sampling will be used to recruit key LTCH stakeholders (directors, administrators, and IT support). In stage 3, the findings from stages 1 and 2 will be triangulated and interpreted to develop a working framework for WPT usage within LTCHs.

**Results:**

Data collection will begin in fall 2023. The findings emerging from this study will provide insights and understanding about how the factors, barriers, and facilitators to embedding and spreading WPT in LTCHs may benefit or negatively impact older adults in LTCHs, family caregivers, and staff and administrators of LTCHs.

**Conclusions:**

The results of this research study will provide a greater understanding of potential approaches that could be used to successfully integrate WPTs in LTCHs. Additionally, benefits as well as challenges for older adults in LTCHs, family caregivers, and staff and administrators of LTCHs will be identified. These findings will help increase knowledge and understanding of how WPT may be used to support social connectedness between older adults in LTCHs and their family members.

**International Registered Report Identifier (IRRID):**

PRR1-10.2196/50137

## Introduction

### The Impact of Restrictions on Social Connectedness

The COVID-19 pandemic and resultant restrictions placed upon Canadians and residents of many other countries (ie, stay-at-home orders and social distancing mandates) significantly impacted elements of many people’s social connections over the last 2 years [1,2]. *Social connectedness*, defined as an individual’s subjective sense of having close relationships with others [3,4] is necessary for health and well-being [5]. During multiple phases of the pandemic, social connectedness was severely compromised for many people both directly and indirectly by restrictions placed on face-to-face engagements [6]. In Canada, older adults in congregate or institutional living environments, such as long-term care homes (LTCHs), were greatly affected during these times [7]. Older adults in LTCHs experienced some of the highest rates of COVID-19 mortality and morbidity of any population group [8,9]. Along with the systematic failure of some LTCH facilities [10], almost all LTCHs were mandated to implement extreme restrictions on visitors and staff, as an emergency infection control [11]. These drastic measures increased isolation and decreased the emotional well-being of older adults in LTCHs [6,12,13].

### Progression of Social Isolation Impact on Older Adults

Before the COVID-19 pandemic, older adults in LTCHs were at risk of experiencing social isolation due to a variety of factors such as challenges with building new relationships, decreased autonomy, and geographical constraints on maintaining face-to-face or in-person connections with friends and family [14]. In older adults, social isolation is associated with negative health impacts such as reduced motor function, depression, cognitive decline, and mortality [15-19]. Similarly, loneliness is also implicated in health declines [20]. As people age, their likelihood of experiencing social isolation and loneliness increases [21,22]. In the United States, upwards of 40% of people older than 60 years reported feeling lonely [23]. In Canada, older adults also report elevated rates of loneliness and social isolation [24]. Moving to LTCHs can increase older adults’ likelihood of being lonely or socially isolated with reported rates of loneliness in older adults living in LTCHs varying from 22% to 75% [20,25,26].

With the start of the pandemic, social connectedness among older adults within LTCHs was severely compromised both directly and indirectly by restrictions placed upon visitors and other infection control measures [27]. This physical isolation of older adults in their rooms thereby compounded any preexisting impacts of isolation [6]. Detrimental impacts on older adults’ mental health associated with quarantine measures include emotional disturbance, insomnia, and low mood [28,29]. While these visitor restrictions were implemented in good faith as an effort to mitigate the spread of COVID-19, many older adults during the height of the pandemic died alone, with little to no connection with their family members or friends [30].

In the initial stages of the COVID-19 pandemic, research findings suggested that older adults may be less vulnerable to detrimental mental health effects of the disease and associated health measures, than their younger peers [30,31]. However, with time, additional studies indicated that the impacts of COVID-related restrictions and the resultant social isolation will have long-lasting repercussions on older adults’ health and well-being [27]. Furthermore, the protracted restrictions associated with the ongoing nature of the pandemic continue to negatively impact the physical and mental health of older adults and their family caregivers [9,12,30]. In Canada, during the first wave of the COVID-19 pandemic, when families were prohibited from in-person visits, there were 7260 deaths of older adults across LTCHs and retirement homes, representing 79% of all COVID-19 deaths [7]. Consequently, during the height of the pandemic, many older adults died isolated and alone [30-33]. Since that time, the policy changed first resulting in modified visitor restrictions that allow family members to be together in palliative circumstances and then removing visitor restrictions altogether [34]. However, challenges relating to the social isolation of older adults within LTCHs remain.

As COVID-19 led to widespread limitations on in-person gatherings and for a time halted in-person visits to LTCHs, attention turned to technology as a means to communicate and facilitate social connectivity between family members and older adults [35]. As we move forward from the pandemic it is critical to develop robust systems now, to mitigate the harmful unintended side effects (eg, decreased social connectedness and well-being) of infection control policies.

### Web-Based Presence Technology

Web-based presence is the use of networked digital telecommunications technology to create the impression that a user is present in another environment [36]. Digital apps (eg, Zoom [Zoom Video Communications] and FaceTime [Apple Inc]) provide web-based face-to-face connection and may support social connectedness by providing meaningful social engagement in addition to being a point of access to community environments for older adults [37]. For LTCHs, web-based presence technology (WPT) has the potential to support social connectedness as a supplement to in-person engagement or a stand-in during outbreak situations such as the current COVID-19 pandemic. Acknowledgement of this potential has been highlighted by the COVID-19 pandemic, which has been a catalyst for myriad and lasting social changes, including the vastly accelerated use of WPT for communication in people’s personal and professional lives. However, the general uptake of WPT across LTCHs has lagged behind other sectors [38] for reasons including age-related bias about older adults’ physical and cognitive ability to use technology, costs of equipment, and a lack of education and support of staff, family, and older adults to use technology devices such as tablets or other mobile devices [39].

Early efforts to explore the application of technology within LTCH settings focused on aspects such as resident safety. However more recently, the role of technology to support social connectedness is also being investigated [40]. Emerging findings suggest that challenges of implementing WPT in LTCHs include limitations in staff shortages, training for staff on the use of WPT, dated LTCH building infrastructure, funding to support additional staffing and technology equipment, and processes supporting consistent use of WPT [41]. Addressing these challenges entails more than just the provision of additional funding. Instead, it asks for an enhanced systemic and context-specific understanding of technology implementation [42]. This understanding has to be cocreated with all relevant LTCH stakeholders (eg, residents, family members, staff, and administration) to effectively address user needs as well as financial, operational, and administrative constraints.

WPT can provide family members of older adults in LTCHs with the opportunity to visually observe the well-being of the older adult in real time. Visual confirmation of these older adults’ well-being can contribute to family members’ trust and confidence in the care being provided by LTCH staff [43]. Admittedly, WPT is not a panacea for fostering social connectedness among older adults in LTCHs [44]. However, it may be profoundly important to supplement in-person activities with *hybridized web-based and in-person approaches* for social connectedness in the context of distancing measures or other constraints on in-person engagement.

### Objectives

Given the potential benefits of WPT within LTCHs and the need to understand associated shortcomings, the proposed research goal is to explore experiences regarding the use of WPT in support of social connectedness between older adults in LTCHs and their family members, and to identify the contextual factors that must be addressed for successful WPT implementation in LTCHs. This study has 3 aims. First, to explore how older adults in LTCHs, their family members, and LTCH staff members experience, benefit from, and envision the role of WPT to support social connectedness in LTCHs. Second, to interview key stakeholders such as managers and directors of LTCHs, and to examine LTCH policy, funding, management, and operations in order to identify institutional challenges and facilitators impacting the uptake and spread of WPT within LTCHs. Third, to triangulate the findings from stages 1 and 2 to develop a framework that can inform the formal implementation of WPT in support of social connectedness within LTCH**.**

## Methods

### Study Team

The faculty team recognizes that there is an implicit bias against some groups’ progression to academia’s higher ranks. Our faculty team is deeply committed to equity and diversity in recruiting, hiring, and training students. This research team will comprise emergent and seasoned scholars and researchers and a research assistant who is a graduate student at the university where the principal investigator is employed.

### Approach

#### Overview

This study will use a qualitative multimethod research design conducted in 3 stages. The multimethod design will be informed by the Technology Acceptance Model (TAM) and entail the use of qualitative description using content analysis (stage 1) and thematic and document analysis methodologies (stage 2). The overarching objective will be to triangulate the findings from stages 1 and 2 to create a working framework to inform the implementation of WPT in LTCHs. Stage 1 is focused on data collection through in-depth interviews with stakeholders (older adults living in LTCHs, their family members and LTCH staff) to inform an initial understanding of the perceived usefulness, ease of use, challenges, attitude toward, and human resource availability to support social connectedness using WPT. Stage 2 will involve the examination of relevant documents (eg, information technology and operational policy documents, budgetary documents and training manuals) and in-depth interviews with key LTCH administrators such as directors and managers as well as salient staff (eg, information technology) that will describe the LTCH environment, its functioning, and regulations to develop an understanding of the institutional factors that have a bearing on potential web-based presence implementation. In stage 3, the data from stages 1 and 2 will be used to triangulate the findings and interpret them to develop a working framework for WPT implementation within LTCHs.

#### Stage 1: Interviews and Framework Development

##### Design

The first stage of this study will use qualitative description to explore how older adults in LTCHs, their family members, and LTCH staff experience and understand the use of WPT in support of the social connectedness of older adults in LTCHs [45]. The outcome of this exploratory enquiry will be combined with the outcome of stage 2.

##### Ethical Considerations

As the initial step of stage 1, ethics approval for the proposed study will be sought from the applicable research ethics boards (Western University Health Science Research Ethics Board). Once ethics approval has been obtained, data collection will be initiated. The research team anticipates beginning the participant recruitment phase in late autumn 2023.

The principal investigator will manage all data generated with this research to ensure effective data use and security. Standardized data file naming, storage (including metadata) and backup procedures will support data sharing and protect the data against catastrophic loss. Data will be stored on a password-protected university server to protect against unauthorized access, in keeping with research ethics board requirements (ID#2023-121993-78969).

##### Participants

To conduct the interviews in stage 1, we will use purposeful and maximum variation sampling to recruit a range of older adults, family members (30 participants) and staff (15 participants) within several LTCH settings with a total recruitment goal of approximately 45 participants [46]. A review of the literature on sample size across 55 qualitative descriptive studies found that about half of studies (24 studies) had a sample size ranging from 8 to 20 participants and approximately 15% (8 studies) of included studies had a sample size of up to 50 participants [46]. Therefore, a total sample size of 45 for stage 1 is deemed to be congruent with other research conducted using a qualitative descriptive method. Data collection and analysis will take place simultaneously and will continue until the data provides a rich description of the participants’ experience in using or supporting the use of WPT for the purposes of social connection. It is expected that data collection will conclude once data saturation has been obtained across the range of participants [47]. Participants will be recruited from 3 LTCHs (anonymized). Given the goal of gaining a holistic understanding of the role of WPT implementation in LTCHs, we hope to recruit a broad range of participants (older adults, family members and staff including, registered practical nurses, registered nurses, personal support workers, and recreation therapists).

Inclusion criteria for this stage will be English speaking and the ability to participate in a one-on-one interview using Zoom technology. Potential older adult participants with mild cognitive decline living in LTCHs or receiving outpatient care will be assessed for suitability to participate in this study by LTCH staff first before any study information will be shared with them. Exclusion criteria applied will be the inability to converse in English and advanced cognitive decline.

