##### Setting

Individual in-depth interviews with older adults, their family members, and LTCH staff will take place in-person, via phone, or Zoom call depending on participant preferences and applicable COVID-19 restrictions at an agreed-upon date and time.

After the screening and deeming an older adult eligible to participate in this study, a research assistant will connect with a recreational therapy department staff or a caregiver in order to assist older adult participants with setting a study interview appointment, securing a quiet room, accessing an electronic device at their LTCHs, and helping them join a Zoom meeting to participate in an interview at an agreed upon date and time.

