##### Data Collection

We will conduct semistructured in-depth interviews with a range of older adults, family members, and staff in several LTCHs. The purpose of conducting these interviews will be to explore participants’ perceptions of how WPT has been used and can be used, and to identify potential barriers to supporting social connectedness between older adults and family members within LTCH settings using WPT. Interview questions will be informed by extended the TAMs as widely applied to questions of health technology implementation [49-51]. The TAM and its extensions are based on 2 belief constructs: perceived technology usefulness and perceived ease of technology use [50,51]. Building on these constructs, a range of interview questions tailored for type of participant (staff, older adult living in LTCHs, and family member) will be posed to participants (eg, can you describe your experience with using technology such as smartphones or tablets for speaking with your family). For a full list of interview questions please see Multimedia Appendix 1. In addition to in-depth interviews, observational field notes will be kept throughout this study thereby enhancing the data set [52].

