##### Data Analysis

Data will be analyzed using directed content analysis, a qualitative analytic technique characterized by a structured stepwise process of coding the data and organizing it into categories or themes [53]. The goal of the analysis will be to provide the initial data for a framework to guide web-based presence implementation in LTCHs. As such, the key constructs of the TAM, perceived usefulness and ease of use of technology, will serve as initial codes to guide analysis. Data that do not lie within one of the key codes will be labeled with a new code and organized into new categories or organized depending on their suitability as subcategories under the initial codes [53]. Throughout the entire sampling and data collection process, data analysis will be conducted in a concurrent and iterative process. Interviews with participants (in-person, via phone or Zoom depending on participant preferences and applicable COVID-19 restrictions) will be audio recorded, transcribed verbatim prior to analysis. Study rigor will be ensured through member checking, verifying data by contacting a subset of participants a second time to verify their intended meaning [54]. In addition, those engaged in the research process will practice reflexivity, acknowledging biases they may introduce to the research, and other strategies such as ethical conduct and ensuring the trustworthiness (eg, confirmability of data through triangulation between interviews and field notes) of this study data will be used [55].

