### Limitations

The proposed multistage approach and methodological triangulation will require the engagement of multiple stakeholders. Potential limitations may include challenges associated with conducting interviews with older adults living in LTCHs who may have cognitive or physical conditions that could limit their participation in in-depth interviews. Additional support from family members, LTCH staff or researcher staff may be required to facilitate interviews with older adults. Researchers will use flexible approaches to interviewing including in-person and zoom interviews, accommodating interview times and an honorarium to recognize their time and contribution. Researchers will also use strategies that can support older adults’ participation such as providing documentation in larger font size and providing a list of questions ahead of time.

The data obtained through qualitative description will consist of subjective perceptions and recollections of using technology for social connectedness and therefore may be biased toward a particular type of experience. Direct user observations, attained using an ethnographic approach, might be able to produce data that have a lower likelihood of being biased toward memorable experiences. However, actualizing this approach within LTCHs would be very challenging to practically implement.

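### Stage 1 makes ability to be interviewed on Zoom an entry condition, although Zoom is an example of the technology under study and other interview modes are planned

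*Protocol article*

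**What the plan says.** The eligibility rule is in Methods, Stage 1, Participants: "Inclusion criteria for this stage will be English speaking and the ability to participate in a one-on-one interview using Zoom technology". It covers every stage 1 group (residents, relatives and staff) and names no other mode. The exclusion sentence in the same section does not mention Zoom: "Exclusion criteria applied will be the inability to converse in English and advanced cognitive decline".

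The Introduction, under Web-Based Presence Technology, places Zoom within the technology being studied: "Digital apps (eg, Zoom [Zoom Video Communications] and FaceTime [Apple Inc]) provide web-based face-to-face connection".

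Three other places describe how interviews will be held:

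- **Stage 1, Setting:** individual interviews "will take place in-person, via phone, or Zoom call depending on participant preferences and applicable COVID-19 restrictions". For residents found eligible, the same section describes help with "accessing an electronic device at their LTCHs, and helping them join a Zoom meeting to participate in an interview".
- **Stage 1, Data Analysis:** "Interviews with participants (in-person, via phone or Zoom depending on participant preferences and applicable COVID-19 restrictions) will be audio recorded".
- **Discussion, Limitations:** "Researchers will use flexible approaches to interviewing including in-person and zoom interviews", offered as an accommodation for older adults whose conditions might limit participation.

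Stage 1, Data Collection gives one purpose of the interviews as "to identify potential barriers to supporting social connectedness between older adults and family members within LTCH settings using WPT".

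**The concern.** There are two linked problems. The first is internal consistency. Interviews in person or by phone require no ability to use Zoom, yet under the eligibility sentence those modes are open only to people who could also have been interviewed on Zoom.

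The second is selection on the subject of the study. Stage 1 asks how easy WPT is to use and what stands in its way, and entry depends on being able to take part through one form of WPT. People at the hardest end of that range would be missing as direct informants. Stage 1 insights shape the stage 2 interview guide, and both stages feed the stage 3 framework, so a gap at entry would carry through to the final product.

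**Working it through.** No figure in the plan bears on this point and no formula applies. The check sets the relevant sections side by side.

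1. **Is Zoom part of what is studied?** Yes. It is the first app named in the section that introduces WPT.

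2. **Is difficulty with WPT a target of stage 1?** Yes. Data Collection makes barriers a purpose of the interviews. Data Analysis takes perceived usefulness and perceived ease of use as the initial codes. A rule that selects on ability to take part by Zoom narrows the range seen on the second of these.

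3. **Does the rule fit the interview modes?**

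| Section | Modes | Zoom ability needed? |
|---|---|---|
| Stage 1, Participants | Zoom only | Yes |
| Stage 1, Setting (general) | In person, phone, Zoom | Only for Zoom |
| Stage 1, Setting (residents' route) | Zoom | Yes, with help |
| Stage 1, Data Analysis | In person, phone, Zoom | Only for Zoom |
| Limitations | In person, Zoom | Only for Zoom |

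The eligibility sentence does not fit the general statement in Setting, nor Data Analysis, nor Limitations. The only practical route spelled out for residents is the Zoom one.

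4. **Who applies the rule?** According to Screening Process, staff of the partner organizations identify suitable people and pass on the study information. Someone they judge ineligible under the written criterion would not be approached, and the researchers might never learn of that person.

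5. **Who is excluded if the rule is applied as written?** The help in Setting is described as following a finding of eligibility, but that order of events does not show that eligibility is judged without help. On the reading most favourable to the plan, ability means ability with assistance. The people excluded are then those who cannot take part by Zoom even with a device and a helper, yet could speak to an interviewer in the room or by phone. The Discussion itself names arthritis, visual impairment and neurodegenerative disease as conditions that may call for adaptive technology or extra assistance. Cognitive limits short of advanced decline belong here too, since only advanced decline is a stated exclusion.

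6. **How large is this group?** The stage 1 target is 30 older adults and family members plus 15 staff, 30 + 15 = 45. The article does not divide the 30 between residents and relatives and gives no share of residents unable to take part by Zoom. The size cannot be derived, and any percentage would be a guess.

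**The case against.** The strongest defence is that the criterion asks for ability to take part, not for independent operation or past use. Setting provides a device and someone to help join the call, and Limitations expects support from family, home staff or researchers. A resident without a device, experience or a usual helper may therefore still qualify. This stands, and it confines the concern to people who cannot take part by Zoom even with that help.

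A reader might infer that everyone who faces the barriers under study is screened out. The article does not support that. The Introduction lists staff shortages, training, building infrastructure, funding, equipment cost and age-related bias, none of which depends on whether the interviewee can use Zoom. Staff and relatives can describe residents who cannot use it, and stage 2 examines institutional barriers through stakeholder interviews and documents. A reader might also infer that barriers will be undercounted by some stated fraction. This is purposeful qualitative description, which estimates no prevalence, so the loss is in the range of first-hand accounts.

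Two further defences carry less weight. Zoom ability could be meant as a fallback under COVID-19 restrictions, but the article does not say so, and the phone is already a remote alternative. The flexible modes may reflect what will happen in practice, in which case the fault is mainly one of wording. That is possible, but the screeners have the written criterion to work from. Limitations acknowledges that conditions may restrict participation but does not mention the Zoom requirement.

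**Conclusion.** The point holds in a bounded form. The Zoom criterion contradicts the interview modes given in Setting, Data Analysis and Limitations. Applied as written, it removes the direct testimony of people who cannot take part by Zoom even with assistance, against the maximum variation aim, and leaves only indirect evidence about them from staff and relatives. This rests on two assumptions: that partner-home screeners follow the criterion as worded, and that such people exist among those otherwise eligible, which the authors' own discussion of impairments makes plausible. If screeners instead follow the flexible modes, the effect is small and the defect is one of drafting. Correction is worthwhile in either case, because it costs little and selection at entry cannot be repaired after recruitment.

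**What to change.** - **Stage 1, Participants:** replace the reference to Zoom technology in the inclusion criterion with *in person, by phone or by Zoom, with assistance if needed*.
- **Stage 1, Setting:** beside the Zoom route for residents, describe an in-person or phone route.
- **Optional:** record interview mode and prior WPT use, and use them to guide maximum variation sampling. The contradiction is resolved without this step. A formal comparison of categories by mode is not needed; with about 45 people in several roles, the mode groups would be small and self-selected.

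The cost is a wording update with the ethics board and some interviewer travel to the three homes, which the plan already allows for by offering in-person interviews. The optional recording adds a few items per participant.

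### The stage 1 eligibility text names older adults receiving outpatient care as potential participants and requires no LTCH residence, although the rest of the protocol places the older adults in LTCHs

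*Protocol article*

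**What the plan says.** All references are to the protocol article. In Methods, stage 1, Participants, the sentence on suitability assessment covers "Potential older adult participants with mild cognitive decline living in LTCHs or receiving outpatient care". LTCH staff assess these people before any study information is shared with them.

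The formal criteria stand on either side of that sentence. Before it: "Inclusion criteria for this stage will be English speaking and the ability to participate in a one-on-one interview using Zoom technology". After it: "Exclusion criteria applied will be the inability to converse in English and advanced cognitive decline". Neither mentions where an older adult lives. The same section gives the recruitment source: "Participants will be recruited from 3 LTCHs (anonymized").

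The Objectives section states aim 1 as "to explore how older adults in LTCHs, their family members, and LTCH staff members experience, benefit from, and envision the role of WPT". Aim 2 is to "identify institutional challenges and facilitators impacting the uptake and spread of WPT within LTCHs", and aim 3 is to "develop a framework that can inform the formal implementation of WPT in support of social connectedness within LTCH". The stage 1 Design section describes the use of WPT "in support of the social connectedness of older adults in LTCHs".

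**The concern.** The eligibility text and the stated study population do not match. Taken literally, an English-speaking older adult with mild cognitive decline who receives outpatient care and can manage a Zoom interview meets every listed criterion without living in an LTCH. Aim 1, which stage 1 serves, is about older adults in LTCHs.

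The study asks how WPT works under LTCH conditions. The Introduction names these as staff shortages, staff training, dated buildings, funding for staffing and equipment, and restrictions on visitors. Someone who does not live in an LTCH cannot describe being a resident under those conditions. Their account would still enter the same directed content analysis, inform the stage 2 interview guide and pass into the stage 3 framework. A reader of that framework could not tell which parts came from residents.

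**Working it through.** No arithmetic applies. The check compares the eligibility sentence with every other place that describes the older-adult participants.

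1. **Does the sentence set outpatients apart from residents?** Yes. It joins the two groups with or, so outpatient care is an alternative to living in an LTCH.

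2. **Do the listed criteria remove non-residents?** No. Inclusion covers language and ability to be interviewed by Zoom. Exclusion covers language and advanced cognitive decline. Residence appears in neither.

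3. **Where do other sections place the older adults?**

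| Section | Older adults described as |
|---|---|
| Objectives, aim 1 | In LTCHs |
| Approach, Overview | Stage 1 stakeholders living in LTCHs |
| Stage 1, Design | In LTCHs |
| Stage 1, Participants (sampling and recruitment sentences) | Recruited within LTCH settings, from 3 homes |
| Stage 1, Screening Process | Residents, assessed by the homes' regular cognitive screening |
| Stage 1, Setting | Helped to reach a device at their own LTCH |
| Stage 1, Data Collection | One of three participant types, living in LTCHs |
| Results and Conclusions | In LTCHs |

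4. **Is the outpatient group explained anywhere?** No. The term occurs once. The article gives it no definition, rationale, recruitment route or role in the analysis. Cognitive status bears on eligibility, yet the only cognitive screening described is that of residents.

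5. **What would happen to such data?** Stage 1, Data Analysis describes a single directed content analysis with perceived usefulness and ease of use as initial codes. It does not separate participants by living situation. Stage 2, Data Collection uses stage 1 insights to build its interview guide, and stage 3 combines both stages in the framework.

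6. **Can the share be sized?** No. The figure of 30 stands beside older adults and family members together, next to 15 staff (30 + 15 = 45). There is no separate count of older adults and no number or cap for outpatients.

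**The case against.** The strongest defence is that the protocol, read as a whole, samples LTCH residents and contains one stray phrase. Recruitment is from three LTCHs, the interview questions are tailored to a participant type living in LTCHs, and the screening and logistics assume residents. The phrase also sits in a sentence about a check made by LTCH staff before study information is shared, not in the list of criteria.

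Much of this stands. The weight of the text points to residents, so a reader who infers an open door to any share of outpatients goes further than the article supports. But a recruitment source is not a residence criterion. If it did exclude outpatients, the phrase would have no function and should still go. A sentence about a suitability check still treats those it names as potential participants.

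A second defence is that outpatient care is undefined and, since LTCH staff do the assessing, may mean a service linked to the partner homes. With maximum variation sampling, a wider group might even be deliberate. Both are possible, and for that reason the authors should have the option of defining the group instead of deleting it. The article says neither, and the wording still distinguishes these people from those living in LTCHs.

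**Conclusion.** The point holds as an inconsistency within the eligibility text. Followed as written, it could admit people outside the aim 1 population, and nothing in the described analysis would keep their accounts apart. It is worth correcting because staff at the partner homes identify and assess candidates and need an unambiguous rule.

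Its size is unknown. The conclusion rests on one assumption: that at least some people receiving outpatient care do not live in an LTCH, which is what the or implies.

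Three stronger readings are not supported:

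- A reader might infer that outpatients would be more able and so make WPT look easier to use or support. The article says nothing about their ability, and the sentence concerns people with mild cognitive decline in both groups. No direction of bias can be claimed.
- A reader might put a figure on the affected share. Without a count of older adults or outpatients, any such figure would be invented.
- A reader might say that all three aims name residents as the group studied. Only aim 1 does. Aim 2 concerns LTCH stakeholders and institutional factors, and aim 3 concerns a framework. Both are limited to LTCHs, but they do not define the older-adult sample.

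**What to change.** In stage 1, Participants, remove the reference to outpatient care and add an inclusion criterion that older-adult participants must be living in one of the participating LTCHs.

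If the group is intended, keep it but define what outpatient care means here, state how these people are recruited and cognitively screened, and analyse their accounts separately from residents' accounts before anything passes to stage 2 or the framework.

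The first option costs a one-sentence edit and a slightly smaller recruitment pool. The second costs a few more sentences and a separate strand of analysis. Either is best settled before recruitment starts.
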